# An AI-based patient-specific clinical decision support system for OA patients choosing surgery or not: study protocol for a single-centre, parallel-group, non-inferiority randomised controlled trial

**DOI:** 10.1186/s13063-022-07039-5

**Published:** 2023-01-12

**Keywords:** Artificial intelligence, Machine learning, Randomised controlled trial, Cost-effectiveness, Clinical decision support system, Total hip replacement, Total knee replacement, Osteoarthritis, Patient-reported outcomes

## Abstract

**Background:**

Osteoarthritis (OA) affects 20% of the adult Danish population, and the financial burden to society amounts to DKK 4.6 billion annually. Research suggests that up to 75% of surgical patients could have postponed an operation and managed with physical training. ERVIN.2 is an artificial intelligence (AI)-based clinical support system that addresses this problem by enhancing patient involvement in decisions concerning surgical knee and hip replacement. However, the clinical outcomes and cost-effectiveness of using such a system are scantily documented.

**Objective:**

The primary objective is to investigate whether the usual care is non-inferior to ERVIN.2 supported care. The second objective is to determine if ERVIN.2 enhances clinical decision support and whether ERVIN.2 supported care is cost-effective.

**Methods:**

This study used a single-centre, non-inferiority, randomised controlled in a two-arm parallel-group design. The study will be reported in compliance with CONSORT guidelines. The control group receives the usual care. As an add-on, the intervention group have access to baseline scores and predicted Oxford hip/knee scores and HRQoL for both the surgical and the non-surgical trajectory. A cost-utility analysis will be conducted alongside the trial using a hospital perspective, a 1-year time horizon and effects estimated using EQ-5D-3L. Results will be presented as cost per QALY gain.

**Discussion:**

This study will bring knowledge about whether ERVIN.2 enhances clinical decision support, clinical effects, and cost-effectiveness of the AI system. The study design will not allow for the blinding of surgeons.

**Trial registration:**

ClinicalTrials.gov NCT04332055. Registered on 2 April 2020.

## Background

Osteoarthritis (OA) is a major public health concern worldwide. A global burden of disease study of OA showed that cases increased 113.25% from 247.51 million in 1990 to 527.81 million in 2019 [1]. Anatomic, site-specific, age-standardised prevalence rates have increased for knee and hip OA, and the estimated annual percentage changes are 0.32 and 0.28, respectively [1]. Osteoarthritis is associated with pain, disability and loss of function for patients; therefore, healthcare providers and policymakers should be aware of the increasing burden of the disease [1]. International clinical guidelines for the treatment of OA recommend physical training and complementary pharmacological treatment as first-line treatment modalities, and when these options no longer have a positive effect, assessment for joint replacement surgery is advised [2]. In 2014, more than 370,000 primary total hip replacements (THR) were undertaken in the USA and 37,000 were conducted in Australia and 97,000 in the UK in 2017 [3]. In 2008, the USA and Australia conducted 6,485,000 and 359,000 total knee replacements (TKR), respectively, and the UK performed 793,000 surgeries in 2009 [4]. In Denmark, OA affects 20% of the adult population with an economic burden to society of DKK 4.6 billion per year [5, 6]. Although pain symptoms can be managed with pharmaceuticals, and physical training may slow disease progression, nearly 11,000 and 10,500 hip and knee replacements are performed annually in Denmark [2, 7, 8].

However, for all the mentioned treatment options, the guidelines do not provide clear guidance about when surgery is most beneficial for the individual patient. Consequently, under or over utilisation of healthcare resources may occur [2, 9–11]. Research suggests that up to 75% of patients could have postponed surgery and managed with physical training instead [12]. Additionally, matching patients’ expectations with achievable changes in function level can be challenging, which might help explain why up to 28% of the patients who undergo THR or TKR are dissatisfied post-surgery [13, 14]. The limited time to provide tailored treatment options and the adjustment of patients’ unrealistic expectations both prompt the high proportion of dissatisfied patients [13]. Providing access to predicted patient-specific outcomes, including health-related quality of life (HRQoL) consequences, before surgery may be important to improve decision-making and patient satisfaction. One solution to provide this information could be artificial intelligence (AI).

ERVIN.2 is an AI-based clinical decision support system designed to support patient involvement in decisions concerning knee and hip replacement. The system allows for the patient and surgeon to compare real-time (the reported scores on the day of consultation) and one-year prediction scores, negative or positive, in function and pain (OKS/OHS) and HRQoL (EQ-5D-3L) for the two treatment alternatives; surgery or non-surgical treatment. The purpose of ERVIN.2 is to reduce the number of surgeries and provide a tool to reduce the number of patients who are offered surgery but have no clinical or HRQoL benefits and vice versa, to reduce the number of patients who are not offered surgery but would benefit from it.

A national clinical coordination group of surgeons, physiotherapists, patients, nurses and other experts recommended these outcome measures as usable patient-reported outcome measures for baseline and 1-year follow-up scores [15, 16]. The rationale for using Oxford scores for collecting data is that they are designed to assess function and pain with patients undergoing hip replacement surgery and best validated in a Danish context [17]. ERVIN.2 does not allow for more than one clinical PRO questionnaire to avoid unreliable answers.

The scores are presented in a simple graphical interface, which can be included in the interaction between the patient and the surgeon during consultations. By comparing usual care and an ERVIN.2-based care model, the study aims to investigate if ERVIN.2 enhances clinical decision-making by increasing patient involvement (measured as SDM-Q9 and SDM-doc) without reducing the health (measured as OHS or OKS) of the patients. Therefore, a non-inferiority design is chosen. Furthermore, the aim of the economic evaluation carried out alongside the RCT is to evaluate whether ERVIN.2 is cost-effective compared to usual care. The objective of the present trial protocol is to provide the study design and planned analyses for the RCT and subsequent economic evaluation.

The primary aim of this study is to determine if usual practice (control) is non-inferior to using ERVIN.2 as an add-on to usual practice (intervention) measured by OKS and OHS for patients with OA who are referred to the orthopaedic department to decide if they should have total hip or knee replacement surgery. Secondary aims are to determine the degree of shared decision-making (SDM) by comparing the control and intervention groups as well as conducting a full health economic evaluation.

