#### Primary outcome

The primary outcome measures are OHS and OKS, depending on the indication. Both questionnaires are developed to assess pain and function for patients undergoing hip or knee replacement surgery and are available in Danish-validated versions [21, 22]. The questionnaires are short, 12-item, patient-reported outcome (PRO) questionnaires, including two domains: pain and function with six items each. The questionnaires are reported to be valid, reproducible and sensitive to clinically important changes [23]. Item scores are summed to give a total score between 0 and 48, with higher scores indicating a better outcome [23, 24].

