### Non-inferiority margin

To demonstrate non-inferiority a four points margin is used for both the OHS and OKS scales. Four points are half the size of what is considered to be a clinically relevant difference from the patient perspective [32].

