## Discussion

In this study, we expect no difference in OHS or OKS when using ERVIN.2 as an add-on to usual practice. A study by De Achaval et al. showed potential to improve SDM in patients with knee osteoarthritis, considering TKR measured by using the decisional conflict scale developed by O’Connor. However, the association with changes in the Knee Injury and Osteoarthritis Outcome Score (KOOS) was not covered [38]. Another study achieved inconclusive results when investigating the effect of enhanced SDM on clinical outcome (KOOS or Harris hip score) for patients who were to decide on joint replacement surgery or not [39]. The findings showed a positive impact on knee patients but a negative impact on hip patients. The interventions in the two studies did not use advanced technology such as AI-based software to improve clinical and decision support in orthopaedic surgery [40].

The design of this study does not allow for the blinding of surgeons to reduce bias. The development of ERVIN.1/.2 was based only on data from a single centre, which constituted a limitation concerning generalisability. However, the Danish healthcare system is tax-financed and free for all citizens, and the national quality of THR and TKR is of high quality. Another limitation is that the non-surgical patients can choose different treatment courses after the consultation in the outpatient clinic. The results from this study seek to increase knowledge about ERVIN.2 and whether the use of the clinical decision support systems is associated with an increased sense of SDM, while clinical outcomes in the form of OHS or OKS and QALY remain unchanged. In addition, we seek to investigate whether ERVIN.2 is cost-effective. The results can guide decision-makers by providing transparency about potential health-related benefits for patients and efficient allocation of scarce healthcare resources.

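### The primary non-inferiority hypothesis runs in the wrong direction: it asks whether usual care is non-inferior to ERVIN.2, while the rationale needs ERVIN.2 to be non-inferior to usual care

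*Protocol article*

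**What the plan says.** The hypothesis appears twice in the protocol article, in the same direction both times. In the abstract's Objective: "The primary objective is to investigate whether the usual care is non-inferior to ERVIN.2 supported care". In the last paragraph of the Background, the primary aim is to "determine if usual practice (control) is non-inferior to using ERVIN.2 as an add-on to usual practice (intervention"). The arms are labelled in brackets, so there is no doubt which is which, and the abstract's Methods confirms it: "The control group receives the usual care".

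The reason for the design is given one paragraph before the aim. ERVIN.2 is to improve decision-making through greater patient involvement "without reducing the health (measured as OHS or OKS) of the patients. Therefore, a non-inferiority design is chosen". The Discussion keeps to that intent: "we expect no difference in OHS or OKS when using ERVIN.2 as an add-on to usual practice".

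Two further statements fix the scale and the margin. Primary outcome: "Item scores are summed to give a total score between 0 and 48, with higher scores indicating a better outcome". Non-inferiority margin: "To demonstrate non-inferiority a four points margin is used for both the OHS and OKS scales". The margin section does not say which arm must not fall behind which. The Sample size and Statistical analysis sections name no direction either.

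**The concern.** A non-inferiority claim is directional. Saying that A is non-inferior to B rules out A being worse than B by the margin or more; it says nothing about how much worse B may be than A. The stated aim therefore rules out only that usual care is worse by 4 points, which is the same as ruling out that ERVIN.2 is better by 4 points. It leaves open that ERVIN.2 does harm, of any size.

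Harm is the question the design was chosen to answer. The Background gives reducing the number of operations as one purpose of ERVIN.2, alongside finding patients who are not offered surgery but would benefit. A reader will want to know whether pain and function a year later are worse when the tool is used. If the stated hypothesis is carried into the analysis and report, a positive primary result would be no evidence on that, and a real benefit of ERVIN.2 would count as a failed trial.

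**Working it through.** **Inputs.** SD of change 10.4, 5% significance level, 90% power, 10% drop-out and 130 per arm (Sample size); margin 4 points (Non-inferiority margin); 1:1 allocation (Trial design); expected difference 0 (Discussion); higher score is better (Primary outcome). The article does not say whether the 5% is one-sided or two-sided.

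**Reproducing the plan's sample size.** With margin 4 and true difference 0, at one-sided 5%:

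n = 2 × (1.645 + 1.282)² × 10.4² / 4² ≈ 115.8, so 116 per arm; 116 / 0.9 ≈ 129.

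Using the t distribution, n = 117 and 117 / 0.9 = 130, exactly the stated figure. One-sided 2.5% gives 143, or 159 after drop-out, which does not match. I therefore take one-sided 5% as the working assumption, with 117 evaluable per arm. The formula is the same in either direction when the true difference is 0 and allocation is equal, so the sample size cannot show which direction was meant.

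**The two hypotheses.** Let d = mean(ERVIN.2) − mean(usual care).

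- As written (usual care non-inferior): H0: d ≥ +4, H1: d < +4. Success when the upper bound for d is below +4.
- As the rationale requires (ERVIN.2 non-inferior): H0: d ≤ −4, H1: d > −4. Success when the lower bound for d is above −4.

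**Decision limits.** SE = 10.4 × √(2/117) = 1.36, and 1.645 × 1.36 = 2.24. The written hypothesis succeeds for any estimated difference below 4 − 2.24 = +1.76. The needed one succeeds for any estimate above −1.76. For example, an estimate of −3 has bounds −3 ± 2.24 = (−5.24, −0.76). The upper bound is below +4, so the hypothesis as written is met. But the interval lies wholly on the side of harm and extends past −4.

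**Probability of success.** As written: Φ((4 − d)/SE − 1.645). Needed: Φ((4 + d)/SE − 1.645).

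| True d (ERVIN.2 − usual care) | As written | Needed direction |
|---|---|---|
| −4 | >0.999 | 0.05 |
| −2 | 0.997 | 0.43 |
| 0 | 0.90 | 0.90 |
| +2 | 0.43 | 0.997 |
| +4 | 0.05 | >0.999 |

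At d = −2, for example: (4 + 2)/1.36 − 1.645 = 2.77, giving 0.997; (4 − 2)/1.36 − 1.645 = −0.17, giving 0.43.

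**Sensitivity to the level.** At one-sided 2.5% with the same 117 per arm, the figures (as written against needed) are 0.993 against 0.31 at d = −2, 0.84 for both at d = 0, and >0.999 against 0.025 at d = −4. The pattern is the same.

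**The case against.** The strongest reply is that the article sets out no formal null and alternative hypotheses and no confidence-bound rule. The planned mixed-effects regression gives an estimated difference with an interval, and either bound can be read from it. The rationale and the Discussion show what was meant, so this may be swapped wording that the analysis would put right. A decision rule is also commonly left to a statistical analysis plan, which is not shown.

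Part of this stands. The probabilities above apply only if the stated hypothesis is followed literally, and the absence of a formal rule is not itself a fault here. But the point concerns what the article does state. Naming the arms, calling one non-inferior to the other and giving a 4-point margin already determines which bound is tested. The same order appears in both the abstract and the main text, and the Intervention group section also calls ERVIN.2 the comparator, so this does not look like a single slip. With no other directional statement, the written aim is the only instruction on which bound counts, and the choice could otherwise be made after the data are seen.

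A deliberate reversal, to show that the tool is unnecessary, is conceivable, but it does not fit a design justified by ERVIN.2 not reducing health.

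Two smaller points also stand. A true difference exactly at the margin gives 5% by construction, so the 2-point scenario is the more informative one. And the Trial status section reports 300 recruited, which would leave about 150 × 0.9 = 135 per arm rather than 117; that raises the probability of success at d = 0 to 0.94 in both directions and leaves the contrast as it is.

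**Conclusion.** The concern holds and must be fixed. The primary hypothesis as worded contradicts the article's own reason for choosing a non-inferiority design, and success on it would not show that ERVIN.2 preserves Oxford scores. If ERVIN.2 truly costs 2 points, the written hypothesis succeeds with probability 0.997 against 0.43 in the needed direction; if it truly gains 4 points, 0.05 against above 0.999. The two agree only when the true difference is zero. The contradiction can be read from the text alone. The figures rest on the plan's SD and margin, 117 evaluable patients per arm, a simple two-group comparison, and one-sided 5%, which is inferred because it reproduces 130 per arm. At one-sided 2.5% the conclusion is the same.

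**What to change.** Reword the abstract's Objective and the primary aim in the Background: the aim is to determine whether ERVIN.2-supported care is non-inferior to usual care on the OHS or OKS. State the hypotheses with the margin: H0: mean(ERVIN.2) − mean(usual care) ≤ −4; H1: > −4. Non-inferiority is concluded when the lower confidence bound for ERVIN.2 minus usual care lies above −4. Add the direction to the Non-inferiority margin section, and stop calling ERVIN.2 the comparator in the Intervention group section.

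Make the same correction in any other document that repeats the wording; whether any does cannot be seen from here. Recruitment is reported as complete, so the correction should be dated and made before the randomisation key is revealed to the investigators. If that has already happened, the report should say so.

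The cost is wording only. Sample size, margin, randomisation, data collection and regression model are unaffected.

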## Methods

### Trial design

A single-centre, patient-blinded 1:1 randomised-block controlled two-arm parallel-group non-inferiority trial was conducted from 30.11.2021 to 31.12.2022.

### Study setting

A single-site trial will be carried out at the Department of Orthopaedic Surgery at Aalborg University Hospital, Farsoe. The department performs orthopaedic surgery on patients with OA in their hips and knees. The clinic receives 3000 new referrals for THR or TKR consultations per year, and of these, 1000 patients have joint replacement surgery. The clinic has eight permanent hip and knee specialist surgeons and a varying number of younger doctors in training programmes. The patients are referred by a general practitioner (GP) to the clinic to consult a surgeon about total hip or knee replacement following OA. Only permanent surgeons are included in the trial.

### Eligibility criteria

Patients will receive the first trial information at home by secure e-mail along with an invitation to the clinical assessment. When the patient arrives at the clinic, a designated helper will show him or her to the electronic PRO (ePRO) kiosk and orally inform the patient about the trial. Patients who agree to participate in the trial will sign the informed consent when logging into the ERVIN.2 system. The designated helper will be available in the room when the ePRO is filled out, should any doubts or questions arise. If the patient declines to participate in the trial, their name is registered in a log. If a participant withdraws informed consent, data are not included for analyses or further collection. Trial information and obtainment of informed consent are collected and stored in agreement with Danish legislation. No biological specimens were involved in the study.

## Interventions

### Treatment as usual

The conventional approach to decide if hip or knee replacement should be chosen includes a 30-min consultation in which the surgeon evaluates the need for surgery. This decision is based on the patient’s general health and subjective description of pain and disabilities. Additional health information from the referring GP may also be assessed. The orthopaedic surgeon evaluates x-rays and eventual MRI or CT scans and conducts a comprehensive physical examination focusing on the lower extremities and lower back. The findings and knowledge obtained are discussed with the patient before the decision is made.

### Intervention group

The justification of ERVIN.2 as a comparator is its ability to capture and estimate the baseline and predicted clinical outcomes for OHS or OKS and expected HRQoL for the non-surgical treatment or surgical choice. During the consultation, only the intervention group will have the results from ERVIN.2 as an interface with a graphical presentation of real-time and predicted outcome scores (OHS or OKS and EQ-5D-3L).

This trial builds upon the experiences from using ERVIN.1, which can predict outcomes for surgical choices. The development of ERVIN.1 began in 2013, and the system has been available in the department since 2018. However, its usage is unknown since it is not a part of the usual clinical routine. In 2020, ERVIN.2 replaced ERVIN.1, and this version can predict outcome scores for both surgical and non-surgical choices. The learning datasets used for development and training for ERVIN.1 and ERIN.2 do not differ from the study centre except for the time difference. All hip and knee patients included in the current trial enter data in the ePRO kiosk, including OHS, OKS, and EQ-5D-3L questionnaires. ERVIN.2 combines the ePRO data with data merged from the patient administrative system (PAS) and the electronic laboratory system (LABKA). The merged dataset is then applied in real-time predictive analyses, estimating expected outcome scores for the individual patient [18]. ERVIN.2 then visualises the ePRO data in a shared interface, which shows normalised real-time baseline values and 1-year predictive scores for the expected change in OKS or OHS, ranging from 0 to 100, and EQ-5D-3L scores ranging from 1 to 100 (Fig. 1).

**Fig. 1 Fig1:**
[figure not shown]
Graphical presentation of baseline (real-time) and predicted OKS and EQ-5D-3L score. The *x*-axis = time in years, and the *y*-axis = normalised score scale). The 1- and 2-year predictive scores are shown for the operative choice (red), and 1-year prediction scores for the non-operative choice (blue)

The trial applies a revised version of the prediction algorithm in ERVIN.2, completed by the end of 2020 (publication in progress), which allows for prediction scores related to the conventional treatment. Until now, there is no evidence about the effects of the AI-based decision support system ERVIN.2. However, an evaluation report of ERVIN.1 has confirmed the feasibility and pointed to a large potential benefit for patients and doctors [19]. All intervention surgeons have a one-to-one training session with the project surgeon at the department where the new features are explained and tested before the trial begins. Subsequently, a pilot period of approximately one month was included to adjust for the learning curve. The trial description and flowchart are available in all consultation rooms.

In the inclusion period, surgeons are obligated to present the ERVIN.2 interface during the consultation to those allocated to the intervention group. The intervention is designed to guide the decision on surgery, and the decision will not affect the subsequent treatment. Thus, further attempts to modify or increase adherence to treatment will not be made.

